## Abstract

**Background:**

Living with HIV makes considerable demands on a person in terms of self-management, especially as regards adherence to treatment and coping with adverse side-effects. The online HIV Treatment, Virtual Nursing Assistance and Education (Virus de I’immunodéficience Humaine–Traitement Assistance Virtuelle Infirmière et Enseignement; VIH-TAVIE™) intervention was developed to provide persons living with HIV (PLHIV) with personalized follow-up and real-time support in managing their medication intake on a daily basis. An online randomized controlled trial (RCT) will be conducted to evaluate the efficacy of this intervention primarily in optimizing adherence to combination anti-retroviral therapy (ART) among PLHIV.

**Methods/design:**

A convenience sample of 232 PLHIV will be split evenly and randomly between an experimental group that will use the web application, and a control group that will be handed a list of websites of interest. Participants must be aged 18 years or older, have been on ART for at least 6 months, and have internet access. The intervention is composed of four interactive computer sessions of 20 to 30 minutes hosted by a virtual nurse who engages the PLHIV in a skills-learning process aimed at improving self-management of medication intake. Adherence constitutes the principal outcome, and is defined as the intake of at least 95% of the prescribed tablets. The following intermediary measures will be assessed: self-efficacy and attitude towards antiretroviral medication, symptom-related discomfort, and emotional support. There will be three measurement times: baseline (T0), after 3 months (T3) and 6 months (T6) of baseline measurement. The principal analyses will focus on comparing the two groups in terms of treatment adherence at the end of follow-up at T6. An intention-to-treat (ITT) analysis will be carried out to evaluate the true value of the intervention in a real context.

**Discussion:**

Carrying out this online RCT poses various challenges in terms of recruitment, ethics, and data collection, including participant follow-up over an extended period. Collaboration between researchers from clinical disciplines (nursing, medicine), and experts in behavioral sciences information technology and media will be crucial to the development of innovative solutions to supplying and delivering health services.

**Trial registration:**

CE 11.184 / NCT 01510340

## Background

The morbidity and mortality rates of people infected with HIV has declined dramatically since the advent in 1996 of combination antiretroviral therapy (ART) and the use of appropriate prophylaxis against opportunistic infections [1,2]. Formerly classified as a terminal illness, HIV infection is today considered a chronic disease. Although ART cannot eradicate HIV, existing antiviral therapies suppress viral replication and thus make it possible to maintain and improve the immune function of infected individuals. However, adherence to treatment is key to preventing treatment failure and the development of antiviral drug resistance.

A certain degree of non-adherence might have an effect on treatment outcome, depending on pattern and medication. For example, individuals who skip treatment on consecutive days (sustained interruption) are at higher risk of presenting a detectable viral load than are those who skip an equal number of doses non-consecutively (interspersed missed doses) [3,4]. Furthermore, it has been recognized that, because of their long half-lives and potency, certain types of medication, such as non-nucleoside reverse-transcriptase inhibitors (NNRTIs) and boosted protease inhibitors (PIs), are more forgiving of moderate levels of adherence [5,6]. Notwithstanding, poor adherence remains a major risk factor in virologic failure and the development of resistance [7]. Therefore, developing interventions to boost and sustain ART adherence has become a crucial objective in the field of HIV management.

### Interventions to foster adherence

Treatment adherence immediately arose as a key issue after the introduction of ART. The need to develop appropriate support interventions to foster adherence was crucial at the time, and it remains strong today, despite the fact that regimens have grown simpler [8] (smaller doses, fewer pills) and easier to tolerate over time. After all, ART constitutes a lifetime commitment on the part of the infected individual. Since 2003, the results of pilot studies have demonstrated the feasibility of interventions to influence adherence [9-12], and some interventions evaluated in experimental studies have shown a potential to optimize adherence [13-22]. A systematic review of treatment adherence interventions intended for persons living with HIV (PLHIV) [23] suggested that individual interventions targeting medication management skills were associated with improved adherence outcomes (*n* = 10 studies). In their systematic review of interventions intended to optimize medication adherence among other groups, Haynes *et al*. [24] indicated that only 36 of the 83 interventions examined were associated with improved adherence. Kripalani *et al.*[25] reported similar results in their review focused on a chronically ill group. Of the 37 randomized trials reviewed, 20 produced a significant change in at least one adherence marker, and over half of these interventions (n = 11) had an effect on clinical markers.

In light of these mixed results, Haynes *et al*. [24] stressed the need for novel approaches to support treatment adherence. Recent reviews by Bärnighausen *et al*. [26] and Horvarth *et al*. [27] have suggested that interventions assisted by information and communication technologies, such as text messages sent via mobile phone, could effectively increase adherence in sub-Saharan Africa. Thus, tailored interventions and the use of information technologies open up interesting possibilities for developing innovative interventions geared to optimizing treatment adherence and reaching a broader patient base across vast geographical areas.

### Information and communications technologies: a promising avenue for providing support to people living with HIV

In the field of health education, there is a growing and apparently inevitable tendency to use information and communication technology (ICT), such as web applications and software systems, as interactive means of information transmission [28-31]. These technologies make it possible not only to present a large amount of information in a more user-friendly way, but also for users to access, at their convenience, information better adapted to their own needs. This characteristic greatly facilitates the active learning process at the heart of the development and reinforcement of health behavior self-management skills [32-34].

Tailored interventions are defined as change strategies intended for a given person based on their specific characteristics, identified beforehand through an individual evaluation [35,36]. What distinguishes these interventions is the fact that the change strategy targets the needs of one particular person rather than those of a group, and that the messages and feedback conveyed are adapted to individual factors related to a given health behavior [37]. This makes it possible to achieve more significant results as the person feels more engaged by the messages and in turn engages more readily in the proposed strategies [38-40].

The combined benefits of tailored interventions and of the use of ICT make this type of intervention more effective than traditional health education interventions [34]. Studies have confirmed the efficacy of this type of intervention on the adoption of various health behaviors, including quitting smoking [41-45], reducing the amount of fat in the diet [46,47], increasing the consumption of fruit and vegetables [48,49], and engaging in early cancer detection [50,51]. In the field of HIV, ICT has been used to encourage the adoption of safe behaviors whether in terms of sexual practices or use of syringes [52-56].

In their review of computer-assisted tailored interventions delivered online, Lustria and colleagues [57] identified 30 studies (out of the 503 found between 1996 and 2007) where the applications targeted four health behaviors (nutrition (*n* = 10), physical activity (*n* = 7), tobacco use (*n* = 7), alcohol consumption (*n* = 3)) , as well as ‘other behavior’ (*n* = 3). In their analysis, they sought in particular to describe the mechanisms used to put into operation the concept of tailored interventions and to implement online interventions. They found a wide variety of approaches being used, and highlighted the importance of pursuing research in this domain.

The systematic review (*n* = 24 studies) by Murray *et al*. [58] supported the effects of computer-assisted interventions for individuals living with a chronic condition in terms of knowledge acquisition, changes to health behavior, self-efficacy, perceived social support, and other clinical markers. These technologies have been used for individuals living with asthma [59], diabetes [60-62], heart disease [63-66], and HIV [67,68]. On the whole, what emerges is that these technologies can be used with a variety of groups of different ages [69-73]. The use of different ICTs in the field of health education shows that they are effective in transferring knowledge and developing the skills needed for health promotion and management of the demands inherent to illness [29,30].

Regarding access to these technologies, 175 million adults [74] in the USA reportedly used the internet in 2010 to obtain health-related information. According to the results of a Harris poll, 88% of adults online have searched the web for such information. Moreover, in 2009, Statistics Canada [75] reported that 80% of Canadians 16 years of age or over used the internet at home for personal reasons, and this percentage represented 21.7 million users. These Canadian data also showed that 70% of people used the internet to search for medical information and for health-related purposes (74% of women and 66% of men). In Quebec, the second most densely populated province in Canada, the NETendances survey conducted by CEFRIO-Léger Marketing [76] showed that 79.1% of *Québécois* had used the internet in the previous 7 days.

To date, web applications have been developed to support primary and secondary prevention efforts for tobacco use, physical activity, nutrition, use of certain health examinations, and the adoption of safe sexual behaviors. However, few tailored interventions have used this educational approach in tertiary prevention to support treatment adherence. Living with HIV makes considerable demands on a person in terms of self-management, especially regarding adherence to lifelong therapy and coping with adverse side-effects. PLHIV must play a more active role in this management, thus breaking with the traditional paternalistic health model in which the patient has a more passive role. Instead, the health professional becomes a care partner and mentor who empowers the PLHIV to take charge of the situation. Consequently, it is imperative that innovative ways should be found to provide assistance and follow-up to PLHIV. From this point of view, we believe that the use of ICTs can constitute an effective approach to treatment management by providing PLHIV with support in the form of messages that target and are adapted to their needs. Such virtual follow-up would be complementary to existing clinical follow-up. Given the persistent or long-term nature of ART, finding new ways to support PLHIV who are on such treatment seems an avenue worth exploring.

### Goal

Drawing on the recommendations of the National Institutes of Health (NIH) [77] regarding the four phases of research on interventions in the field of health sciences, we plan to evaluate the efficacy of an online virtual intervention in optimizing adherence to antiretroviral medication intake by PLHIV (phase III). The study will rest on preliminary work (phases I and II) that served to clearly identify the predictors of treatment adherence by PLHIV [78], and will develop and validate the content of the intervention in question [79], and create the corresponding web application [80].

### Preliminary work

Based on a philosophy of empowerment, the HIV Treatment, Virtual Nursing Assistance and Education (Virus de l’immunodéficience Humaine–Traitement Assistance Virtuelle Infirmière et Enseignement; VIH-TAVIE™^a^) web application makes it possible to develop and strengthen the skills needed for PLHIV to self-manage their treatment while boosting their sense of self-efficacy with respect to the daily intake of medication [80]. This application was developed in accordance with the systematic analytic process proposed by Bartholomew *et al.*[81,82], and rests on explanatory and predictive models of health behaviors [79]. The specificity of this application lies in its action mechanism based on Bandura’s theory of behavioral change [83], which targets the development and reinforcement of skills, that is, the individual’s ability to act.

The web application is composed of four interactive computer sessions hosted by a virtual nurse who engages the PLHIV in a skills-learning process aimed at improving self-management of medication intake. The skills covered (motivational, self-awareness, problem-solving, emotion-regulation, social) allow the PLHIV to integrate the therapeutic regimen in their daily routine, manage adverse side-effects, handle problem situations that might interfere with medication intake, interact with health professionals, and mobilize their social support network. Aside from delivering tailored teaching, the virtual nurse refers to the experiences of other individuals who coped with similar situations successfully. During these sessions, the virtual nurse provides feedback and positive reinforcement on the individual’s personal style and methods and on the acquired skills. The interactive system is designed to allow repeated applications and backtracking depending on the individual’s needs. Moreover, at each session, feedback is provided on the significant elements of the previous session. The individual’s profile is personalized as a function of their needs and characteristics, thus giving the profile a tailored fit. Furthermore, the computer innovation underlying the virtual intervention allows to create new pages , thus allowing the system administrator the flexibility to add or modify page models and content depending on the context.

## Methods

### Ethics approval

The study has been approved by the Research Ethics Board of the Université de Montréal and the Research Center of the Centre Hospitalier de l’Université de Montréal.

## Design

We opted for an online randomized controlled trial (RCT) to evaluate the efficacy of the virtual intervention (web application) primarily in influencing ART adherence. Adherence is a behavioral indicator that can be predicted in part by cognitive and affective variables, particularly sense of self-efficacy and attitude towards antiretroviral medication intake [78]. These variables are in turn explained by perceived social support, relationship with health professionals, and absence of adverse effects. These intermediate variables, which are the targets of our intervention, will allow effective change in the short term. They constitute mediators capable of explaining the intervention’s effect on adherence. There will be three measurement times: baseline (T0), after 3 (T3) and 6 months (T6) of baseline measurement. Participants will be drawn from a convenience sample and will be randomly assigned either to an experimental group that will use our web application, or to a control group that will be presented with a list of various websites of interest.

### Hypotheses

The primary hypothesis is that a higher proportion of participants in the experimental group will prove treatment-adherent at T6 compared with the control group. The explanatory hypothesis is that the following variables are mediators that can explain the intervention’s effect on adherence: sense of self-efficacy, attitude towards antiretroviral medication intake, degree of symptom-related discomfort, and perceived social support (T0, T3, T6).

### Sample

We aim to recruit a sample of 232 participants, that is, 116 per group. The PLHIV who will participate in the study must be at least 18 years of age and on ART for at least 6 months. The reason for the latter criterion is that we wish the therapy-management intervention to focus on adherence over time rather than on treatment initiation. Internet access is another inclusion criterion. This will introduce a selection bias in the study; however, the bias will be offset by the inherent value in evaluating an innovative service-delivery method that, in the near future, could reach a vast number of people at low cost and, thus, constitute an important option for providing follow-up to groups with a chronic health problem. In this study, both the experimental group and the control group will be composed of PLHIV with similar characteristics, who have internet access and who use it to obtain information relative to their health condition.

The sample size was estimated based on the studies by Tuldrà *et al.*[84] and Pradier *et al*. [18] carried out with PLHIV, and on the systematic review by Haynes *et al*.
[24] of adherence-related interventions intended for various groups. In the study by Tuldrà *et al*. [84], there was a difference of 25 percentage points between the control group and the experimental group in terms of treatment adherence (69% vs. 94%, respectively). For Pradier *et al.*[18], the proportion of treatment-adherent participants was 58% in the experimental group and 63% in the control group at the start of the study, and 75% and 60% respectively after the intervention. We calculated our sample size on the assumption that the proposed intervention (the web application) will increase the percentage of treatment-adherent participants in the experimental group by 20%. The percentage of treatment-adherent participants at the start of the study will be the same as that reported by Godin *et al*. [78] (that is, 50%), given that our recruitment pool is very similar to theirs. This is a conservative assumption given that the variance in the difference between the two proportions will be larger, with the benchmark proportion set at about 50%. Consequently, the sample size required to detect a difference of 20% (50% treatment-adherent participants in the control group versus 70% in the experimental group) will be larger than for other scenarios with the same 20-point difference. Hence, to detect a difference of 20 percentage points at 80% power and a χ^2^ test two-tailed α value of 0.05, the required sample size is 186 participants, that is, 93 per group. As we are assuming a 20% attrition rate (that is, the same rate seen in the studies by Goujard *et al*. [14] and Tuldrà *et al.*[84]), the sample size has been set at 232 participants. With a sample of 186 participants completing the study, the statistical power will be enough to detect a moderate effect on the intermediate variables. In particular, with *n* = 186, an α value of 0.05 (two-tailed Student’s *t*-test) will allow detection of the difference between the two percentages, corresponding to a standard deviation of 50% and power of greater than 90%.

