### Recruitment and online data collection

The study will be conducted entirely online. The project will be advertised on the websites of resources available to PLHIV, where a hyperlink and a banner will be inserted to redirect parties interested in participating in the online research. The targeted resources include partner clinics, community agencies, and other organizations that deliver teaching, care, treatment, or follow-up to PLHIV. In addition, health professionals and stakeholders will be invited to inform their PLHIV about the study. To promote the project among PLHIV, different communication strategies will be used: 1) traditional methods, such as poster and information brochures; and 2) technological or virtual methods, by advertising the study on websites of organizations (medical clinics, association for PLHIV) that are often visited by PLHIV.

Individuals who will visit the study’s website will view a short video clip of testimonials by a few PLHIV, then they will be given information on the study. After accepting the conditions of the study and consenting to take part in it, they will sign up for the study by providing an email address and a pseudonym. Each participant will be validated through an email address check. Once this step is completed, a hyperlink will be emailed to allow participants to access the first questionnaire online on the website, and only after having completing this questionnaire will they be randomly assigned by the computer system to the experimental group or the control group. Participants in the control group will be invited to consult pre-determined websites that offer information on ART and its associated side-effects. Participants in the experimental group will be offered the virtual intervention through the web application. At 3 and 6 months after the initial measurement, participants will complete the online questionnaires again. A reminder to this effect will be emailed to them in the days prior to the scheduled measurement. Participants will be compensated for their time spent on the study with a gift certificate for each measurement time completed.

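### Half of entrants are expected to meet the adherence endpoint already at T0, and no stated analysis separates gaining adherence from keeping it at T6

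*Protocol article*

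**What the plan says.** **Who enters.** In the Sample section, participants "must be at least 18 years of age and on ART for at least 6 months", and "Internet access is another inclusion criterion". No level of adherence is required. The reason given for the six-month rule is that "we wish the therapy-management intervention to focus on adherence over time rather than on treatment initiation".

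**What is expected at entry.** The same section states: "The percentage of treatment-adherent participants at the start of the study will be the same as that reported by" an earlier study in a similar recruitment pool, namely 50%. That figure also serves as the control rate. On the effect to be detected, the section says: "We calculated our sample size on the assumption that the proposed intervention (the web application) will increase the percentage of treatment-adherent participants". The assumed rise is 20 points, giving 50% versus 70%.

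**What is compared.** Hypotheses and Type of analysis used set the primary comparison as the proportion adherent (at least 95% of tablets) at T6, by a chi-square test. Logistic regression adjusted for baseline characteristics follows only if the groups turn out to differ. The secondary GEE analysis models adherence at T3 and T6. A missing T6 value counts as non-adherent.

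**When T0 adherence is known.** In Recruitment and online data collection, participants complete the first questionnaire, and "only after having completing this questionnaire will they be randomly assigned by the computer system". T0 adherence is thus available to the program that allocates.

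**The aim.** The Background says that "developing interventions to boost and sustain ART adherence has become a crucial objective", which covers both raising and maintaining adherence.

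**The concern.** A participant who is adherent at T0 cannot gain on a binary endpoint that is already met; that person can only keep it or lose it. A participant who is non-adherent at T0 can only gain it or stay without it. The T6 proportion adds the two. A positive result could come from converting non-adherent people, from preventing lapse in adherent people, or from a mixture, and these support different statements about whom the application helps. A null result is also hard to read: a real effect confined to the non-adherent half is diluted by the other half.

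T0 adherence is also likely to be a strong predictor of T6 adherence. If allocation does not use it, chance imbalance between the arms adds avoidable noise to the primary comparison.

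**Working it through.** **Inputs.** From the article: 50% adherent at T0; 50% versus 70% at T6; two-sided alpha 0.05; 80% power; 93 per group completing; 20% attrition; 116 per group recruited. Assumed, because the article gives none: the probability of keeping adherence (k) and of gaining it (g) in each arm. The 116- and 58-per-arm figures assume complete data.

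**1. The plan's own figure.** The chi-square sample size with pooled variance and no continuity correction for 0.50 versus 0.70 gives 93 per group, 186 in total (power 80.0%). 186 / 0.8 = 232.5, stated as 232. The sample size arithmetic is sound.

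**2. What the T6 proportion contains.** P(T6) = 0.5k + 0.5g. A 20-point overall difference therefore requires

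(difference in k) + (difference in g) = 0.20 / 0.5 = 40 points.

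Splits that all give exactly 50% versus 70%:

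| k control / exp. | g control / exp. | Difference in g |
|---|---|---|
| 80% / 80% | 20% / 60% | +40 |
| 80% / 90% | 20% / 50% | +30 |
| 80% / 100% | 20% / 40% | +20 |
| 70% / 100% | 30% / 40% | +10 |

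The +10 to +40 range covers control keeping rates of 70% or more with no harm to keeping. Lower control keeping would widen it.

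**3. Dilution.** If the application adds 20 points among T0-non-adherent participants and nothing among the others, the overall difference is 0.5 × 20 = 10 points. Power for 50% versus 60% is 28% at 93 per group and 33% at 116; 80% power would need 388 per group.

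**4. Precision within strata.** With 50% adherent, each stratum holds about 0.5 × 116 = 58 per arm.
- Conversion: power is 93% for 20% vs 50%, 66% for 20% vs 40% and 20% for 30% vs 40%.
- Maintenance: power is 32% for 80% vs 90%.
- Interaction, for the 80/90 and 20/50 split: SE = sqrt[(0.16 + 0.25)/58 + (0.16 + 0.09)/58] = sqrt(0.66/58) = 0.107, so a 95% interval of about ±21 points (1.96 × 0.107) around a true difference of 30 − 10 = 20 points.

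**5. Chance imbalance under simple randomisation.** The SD of the arm difference in T0 adherence is sqrt(0.25 × 2/116) = 0.0657. P(|difference| > 0.10) = P(|Z| > 1.52) = 13%.

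**6. What stratified allocation gains (80/90 and 20/50 split, 116 per arm).** The critical difference of the unadjusted test is 1.96 × sqrt(2 × 0.6 × 0.4/116) = 0.126.
- Unstratified: SE = sqrt[(0.25 + 0.21)/116] = 0.0630; (0.20 − 0.126)/0.0630 = 1.17; power 88%.
- Stratified: within-stratum variances average 0.16 (control) and (0.25 + 0.09)/2 = 0.17 (experimental); SE = sqrt(0.33/116) = 0.0533; (0.20 − 0.126)/0.0533 = 1.39; power about 92%.

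The unadjusted test is then conservative. With no effect (k = 80%, g = 20% in both arms) it uses SE sqrt(0.50/116) = 0.0657 where the true value is sqrt(0.32/116) = 0.0525. This is why the factor belongs in the analysis as well as in the allocation.

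**The case against.** The strongest reply is that nothing here contradicts the stated hypothesis. The article asks whether a higher proportion is adherent at T6 in the experimental arm, and the chi-square test answers that in the population enrolled. Preventing lapse is part of the aim, since the Background names raising and maintaining adherence together and the six-month rule is justified by adherence over time. **This stands.** A diluted effect in a mixed population is the correct answer for that population.

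A reader might infer that the trial cannot show improvement in those who need it. The documents do not support that. T0 adherence is collected, half the sample has room to gain, and the limit applies to the planned T6 proportion, not to the data.

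A reader might also infer that allocation ignores T0 adherence. The article says only that the computer assigns at random; stratification factors may be in the full protocol, which is not shown.

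Nor does the 93% power for conversion show that a trial in non-adherent participants alone would be more efficient. It depends on one assumed split; others giving the same overall result yield 66% or 20%.

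Ordinary chance imbalance is partly covered by the conditional adjusted regression. That rule does not separate gaining from keeping, however. What remains is that the article fixes a pooled endpoint that half the entrants are expected to meet at entry, and describes adherence analyses that do not distinguish the two routes to it.

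**Conclusion.** The point holds as a limit on interpretation and efficiency. The randomised T6 comparison is valid for its hypothesis, and there is no bias. The planned 50% versus 70% is compatible with about +10 to +40 points among T0-non-adherent participants, and the stated analyses would not show which applies. A 20-point benefit confined to that group would probably be missed overall (power 28% at 93 per group). Using T0 adherence in allocation would raise power from 88% to about 92% at 116 per arm under the assumed 80/90 and 20/50 split.

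These sizes rest on the article's 50% at T0, a planning figure from an earlier study, and on assumed keep and gain rates.

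It would go too far to say that any claim of improved adherence must rest on the conversion estimate, because that would subordinate a valid randomised primary result to a half-sample secondary one. Only claims about benefit in people who are non-adherent at the start should rest on it.

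**What to change.** Keep eligibility, sample size and the overall T6 comparison.

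1. For participants still to be randomised, allocate 1:1 within T0-adherent and T0-non-adherent strata, if the program does not already do so. Reflect that factor in the T6 analysis.
2. Before analysis, prespecify two secondary between-arm estimates: conversion to adherent at T6 among T0-non-adherent participants, and maintenance at T6 among T0-adherent participants. Add the treatment-by-T0-adherence interaction.
3. Label these as less precise than the overall result (about 58 per arm in each stratum). State that, under the missing-data rule, a T0-adherent participant who drops out counts as having lapsed.
4. Rest statements about benefit in participants who were non-adherent at entry on the conversion estimate.

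The cost is one rule in the allocation program, one factor in the analysis, two extra estimates and one interaction. No extra participants or data are needed. Data collection began in February 2012 (Trial status), so stratified allocation may reach only later entrants; the secondary estimates can be prespecified at any time before analysis.

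### 50% v 70% is not the most demanding 20-point scenario: control rates strictly between 30% and 50% need slightly more than 93 per group

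*Protocol article*

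**What the plan says.** The Sample section of the protocol article powers the primary comparison on "50% treatment-adherent participants in the control group versus 70% in the experimental group". The calculation is made "to detect a difference of 20 percentage points at 80% power" with a χ² "test two-tailed α value of 0.05", and the result is that "the required sample size is 186 participants, that is, 93 per group". Attrition of 20% raises this to the recruitment target: "We aim to recruit a sample of 232 participants, that is, 116 per group".

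The section then defends the 50% control rate. It says "This is a conservative assumption given that the variance in the difference between the two proportions will be larger" when the benchmark is set at about 50%, and it draws the consequence that the sample size required for 50% v 70% "will be larger than for other scenarios with the same 20-point difference". Neither sentence limits the direction or range of those other scenarios.

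**The concern.** The argument seems to carry a one-proportion fact over to a two-proportion problem. The variance of a single proportion is greatest at 50%. The variance of a difference depends on both proportions, so at a fixed gap it should be greatest when the pair is centred on 50%, not when one member of the pair sits there. If so, some 20-point scenarios need more participants than 50% v 70%, contrary to the text.

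What is at stake is the stated justification, not the number itself. Someone relying on these sentences would conclude that, for a true 20-point effect, a control rate other than 50% leaves power at 80% or better.

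**Working it through.** **Inputs**, all from the Sample section: two-sided α 0.05 (z = 1.960), power 80% (z = 0.842), 1:1 allocation, rates of 50% and 70%, attrition 20%.

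**Formula.** Chi-square test, pooled variance under the null hypothesis, no continuity correction, with p̄ = (p₁ + p₂)/2:

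n per group = [1.960·√(2p̄(1−p̄)) + 0.842·√(p₁(1−p₁) + p₂(1−p₂))]² / (p₂ − p₁)²

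**Step 1: the plan's own figure.** For 50% v 70%, p̄ = 0.60, 2p̄(1−p̄) = 0.48, and the sum of variances is 0.25 + 0.21 = 0.46. Then n = (1.358 + 0.571)² / 0.04 = 93.0, so 93 per group and 186 in total, as stated. 186/0.8 = 232.5, consistent with 232.

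**Step 2: where the variance peaks.** Write the two rates as m − d/2 and m + d/2. The sum of variances is then 2m(1−m) − d²/2. For fixed d this is greatest at m = 0.5, so with d = 0.20 the peak is at 40% v 60%:

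- 50% v 70% (m = 0.6): 0.48 − 0.02 = 0.46
- 40% v 60% (m = 0.5): 0.50 − 0.02 = 0.48
- 30% v 50% (m = 0.4): 0.48 − 0.02 = 0.46, the mirror image of the plan's case

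**Step 3: the requirement at the peak.** For 40% v 60%, n = (1.386 + 0.583)² / 0.04 = 96.9, so 97 per group and 194 completers. 194/0.8 = 242.5, about 243 recruited.

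**Step 4: the range at a fixed 20-point gap.**

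| Control v experimental | n per group before rounding | n per group | Power with 93 per group |
|---|---|---|---|
| 25% v 45% | 88.1 | 89 | 82.1% |
| 30% v 50% | 93.0 | 93 | 80.0% |
| 35% v 55% | 95.9 | 96 | 78.8% |
| 40% v 60% | 96.9 | 97 | 78.3% |
| 45% v 65% | 95.9 | 96 | 78.8% |
| 50% v 70% | 93.0 | 93 | 80.0% |
| 55% v 75% | 88.1 | 89 | 82.1% |
| 60% v 80% | 81.2 | 82 | 85.1% |
| 69% v 89% | 63.9 | 64 | 92.4% |

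The requirement exceeds 93 only strictly between control rates of 30% and 50%; the two endpoints need exactly 93. Just outside them the unrounded requirement is lower (92.2 at 29% and at 51%), although it still rounds up to 93.

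**Step 5: dependence on the formula.** The 40% v 60% case also needs more than 50% v 70% with a continuity correction (107 against 103 per group), with unpooled variance (94.2 against 90.3) and with the arcsine method (96.8 against 92.7).

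**The case against.** The best defence is that the claim is true for the comparison the authors had in front of them. The control rates quoted from the earlier studies in the Sample section are 60%, 63% (at study start) and 69%. At a 20-point gap, 50% v 70% needs the larger sample against each of them: 93 per group against 82 at 60% and 64 at 69%. The text says conservative and about 50%; it does not claim an upper bound. The worst case is also only 4 more per group, and no target or analysis depends on the sentence. All of this stands. It is why the point is minor and why the sentences need a qualifier rather than a different sample size. It does not rescue the wording, which refers to other scenarios with the same gap and sets no limit on them.

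Two stronger readings are tempting, and the document supports neither.

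- A reader might infer that a wrong control rate costs power on both sides of 50%, so that the sample size has no safety margin at all. At a fixed 20-point gap the opposite holds above 50%: with 93 per group, power rises to 85.1% at 60%, 87.3% at 63% and 92.4% at 69%. A loss above 50% appears only if one switches to a constant odds ratio, under which the gap shrinks. The article makes no such assumption, and under it power would rise slightly for control rates strictly between 30% and 50%. The quoted sentence concerns a constant 20-point gap, and the article's own precedent with a 69% control rate reports a 25-point gap; the other shows 15 points (60% v 75%).
- A reader might infer that the trial will in fact be analysed at 40% v 60%, because the section on the type of analysis counts missing T6 adherence as non-adherence. With 20% attrition, 50% among completers does become 0.8 × 50% = 40%, but 70% becomes 0.8 × 70% = 56%. That is a 16-point gap, so it is not one of the scenarios the sentence describes. It is a separate question.

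**Conclusion.** The statement is wrong as written, but the error is small. At a fixed 20-point gap, 50% v 70% needs more participants than control rates above 50% or below 30%, and fewer than control rates strictly between 30% and 50%. The most demanding case is 40% v 60%: 97 per group against 93, or 194 completers against 186, a difference of 8 (8/186 = 4.3%). With 93 per group, power there is 78.3%, about 1.7 points below the 80% intended.

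These figures assume the article's own α, power, allocation and 20-point gap, and the pooled chi-square formula that reproduces its 93. The 186 completers are right for 50% v 70%, and the choice of 50% is conservative relative to the control rates of the cited studies. Severity is minor.

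**What to change.** Reword the two sentences in the Sample section along these lines:

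*The 186 completers are the requirement for 50% v 70%. At the same 20-point gap this exceeds the requirement only for control rates above 50% or below 30%. The most demanding 20-point case is 40% v 60%, which needs 97 per group; there, 186 completers give about 78% power.*

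Keep the recruitment target at 232. The cost is two sentences and a slightly less favourable stated property, with no extra participants and no change to the analysis.
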